##### Nutritional status

The Mini Nutritional Assessment Short Form (MNA-SF) [25] is used for the interview-based screening for undernutrition in geriatric practice. It consists of 6 items assessing decrease in food intake, weight loss and psychological stress/acute disease during the last 3 months and mobility, neuropsychological problems, and body mass index. The total score ranges from 0 to 14, scores < 11 indicate elevated risk for undernutrition.

##### Cognitive function

The Timed Test of Money Counting [26] is a short test to assess manual dexterity and cognitive capacity. The patient is given a purse with separate pockets for coins and banknotes, which contains a predefined amount of money (9.80 Euros as a 5-Euro note, a 2-Euro coin, 2 1-Euro coins, a 50-cent coin and 3 10-cent coins) and is asked to take out all the money and count it. The time the patient needs to perform this task is measured. If the patient does not report the correct amount of money, the examiner gives the feedback that the answer is not correct and the patient is allowed to try again, with the number of attempts and the problems the patient has with this task being recorded. The time measurement is not interrupted while correcting patients. The Timed Test of Money Counting is interrupted after 3 incorrect answers or after 300 s, and in both cases a duration of 300 s is recorded. Values < 45 s indicate independence, 45–70 s increased risk for dependence, > 70 s increased care needs [26].

The Trail Making Test for older subjects (ZVT-G) [27] is the German version of the Trail Making Test A [28]. The ZVT-G was developed for subjects ≥ 55 years of age and is included in the Nürnberger Alters-Inventar [27]. The patient is asked to connect numbers from 1 to 30 in rising order with a pen. The time the patient needs to perform this task is measured. Mistakes shall be corrected immediately without interrupting time measurement. If the patient makes more than 3 mistakes, the test is repeated. If the patient again makes more than 3 mistakes or after a maximum time of 300 s, the test is interrupted, in both cases a duration of 300 s is recorded.

Drawing the interlocking pentagons taken from the Mini-mental state examination (MMSE) [29] is used to assess visual-spatial skills.

The Clock-drawing test [30] assesses higher-level cognitive abilities including visuospatial skills, integrative functions and abstract thinking. The patient is given a sheet of paper with a pre-drawn circle. The experimenter shows where the top of the page is and gives the instructions to put the numbers on the clock and set the time at 10 past 11. The score ranges from 1 to 6, with higher scores reflecting a greater number of errors and more impairment.

Time estimation is assessed with two tasks: First, the patient is asked to estimate how long one minute is with the following instruction: “Please give me a sign when you think one minute has passed, starting now.” The time (in s) is measured until the patient gives the sign. Thereafter, the patient is asked to estimate his/her current length of hospital stay in days with the following instruction: “How long have you been in hospital?” It is noted whether the response is correct and, if not, how many days the response differs from the actual length of stay.

The interview part assessing factors possibly influencing medication adherence is framed by a task that addresses prospective memory, which is a version of the task used in the UK Biobank project [31] modified to increase difficulty. Prospective memory indicates the ability to carry out future intentions at a specific time or in response to a specific event. At the beginning of the specific interview part, patients receive the following instruction: “At the end of this interview part, we will show you colored symbols and ask you to touch the blue triangle. However, to test your memory, we want you to actually touch the orange square instead”. The patients are shown a sheet with 3 different shapes (triangle, square, circle) presented in 3 different colors each (blue, orange, pink). Their first and final answer, the history of attempts, and whether a hint was given are recorded.

The six-item screener [32] is based on the MMSE [29] and comprises temporal orientation (current day of the week, month, year) and short term memory (ability to recall 3 newly learned words). A cut-off of ≥ 3 errors is applied to identify participants with cognitive impairment [32].

##### Personality traits

Personality of the patients is assessed with the Big-Five-Inventory-10 (BFI-10) [33]. This questionnaire is based on the currently most popular model of human personality, the Big-Five model, which assumes 5 abstract personality dimensions (neuroticism, extraversion, openness, agreeableness, conscientiousness). Each of these dimensions is assessed with 2 items, which are scored on a 5-point Likert scale (1 = disagree strongly‚ 2 = disagree a little‚ 3 = neither agree nor disagree‚ 4 = agree a little‚ 5 = strongly agree). Scores are averaged per dimension and thus range from 1 to 5, with higher scores indicating higher expression of the personality trait.

The study is ongoing, patient recruitment has already started. Statistical analysis will take place in the second half of 2022, publication of the full results is scheduled for the first half of 2023.

### Statistical analysis

Patients’ characteristics regarding all variables assessed will be reported as mean ± standard deviation for continuous normally distributed variables, as median (Q1; Q3) for continuous variables which are not normally distributed, and as numbers (%, valid % when values are missing) for categorical variables.

For the video-based evaluation of self-administration of medication, at first 15 raters will rate a small subset of the patient sample to check whether the proposed standardized evaluation form is feasible, objective, and reliable. The agreement between the 15 raters on the ratings for each patient will be evaluated using Kendall’s W for categorical data (single items) and intraclass correlation coefficient for continuous data (sum scores). If the agreement is sufficiently high (≥ 0.8), the total patient sample will be rated by 2 independent raters and agreement will be evaluated with Cohen’s kappa for categorical data and intraclass correlation coefficient for continuous data. To assess test–retest reliability of the video-based evaluation, 30 patients will perform the assessment again after 5 days, and the 2 raters, who rated the total patient sample, will rate patient performance again. Retest reliability will be calculated using Spearman’s Rho for continuous variables and Chi-square for categorical variables.

To evaluate which factors influence the ability to self-administer medication, correlation and regression analyses will be performed. For continuous scores describing the ability to self-administer medication, Spearman’s Rho will be used for analyzing continuous and ordinal factors and Chi-square for analyzing nominal factors. Curve estimation procedure will be used to check whether a linear regression model fits the data in case of bivariate continuous associations and variables will be transformed if necessary. Uni- and multivariable linear regressions models including interaction terms will be calculated to identify which factors influence the ability to self-administer medication to which degree. If linear associations are not met even with data transformation, non-linear regressions will be performed. Missing data will be excluded from analysis listwise. All statistical analyses will be performed using SPSS 22 for Windows (IBM Corporation, Armonk, NY, USA). All statistical tests will be 2-tailed and *p*-values < 0.05 will be considered significant.

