##### Video-based evaluation of self-administration of medication

A new method was developed to assess the ability of patients to self-administer medication in different dosage forms in their original packaging (A tablets, B eye-drops, C oral drops, D insulin pen, E patch, F inhaler). The application of each dosage form is explained via an instructional video. Patients perform the tests to assess their ability to self-administer medication in different dosage forms twice (except inhaler test) in a modified order (group 1: ABCDEFEDCBA, group 2: FEDCBAABCDE) to control for sequence effects. Patients’ performance is video recorded, for each dosage form and each trial a separate video film is taken. The different dosage forms should be applied as follows:

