A TabletsOn the table in front of the patient there are two packs of tablets (one including white tablets in an aluminum blister pack and one including blue tablets in a tablet tube), a pill organizer, and a pill cutter. The patient is asked to put one white tablet each for morning, noon, and evening and one blue tablet for the night into the pill organizer and close the organizer. The patient is then asked to open the pill organizer again, take out the blue tablet, divide it into two halves with the pill cutter, and put one half for the night back into the pill organizer.B Eye-dropsOn the table in front of the patient there is a one-dose ophtiole dispenser. The patient is asked to open the ophtiole dispenser.C Oral dropsOn the table in front of the patient there is a child-resistant dropper bottle and a teaspoon. The patient is asked to open the dropper bottle and drop 10 drops onto the teaspoon.D Insulin penOn the table in front of the patient there is an insulin pen. The patient is asked to dial in 12 units and inject it into a ball.E PatchOn the table in front of the patient there is a packed patch. The patient is asked to unpack the patch, peel off the protective liner without touching the sticky part too much, and apply it to the skin of the arm.F InhalerIf the patient's medication already includes a metered-dose inhaler/dry-powder inhaler, the inhalation technique is evaluated according to the validated scoring system developed by Zambelli-Simões et al. [19]. Thereafter, the inspiratory flow rate is measured for each patient at different resistances using the In-Check Dial G16 (MPV Medical GmbH, Munich, Germany). For this purpose, the patient is asked to breathe in slowly and deeply through the mouthpiece at each resistance setting.

If the patients have difficulties during the self-administration of medication, the experimenter can provide verbal or practical assistance, which is documented.

In 30 patients the assessment is repeated after 5 days to assess test–retest reliability.

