Based on the video recordings, 2 independent raters evaluate the patient’s ability to self-administer different dosage forms of medication with a standardized assessment form. In a pilot phase, the form is presented to 15 different raters to evaluate the video recordings of 3 different patients. If the raters encounter problems leading to low interrater agreement, the form will be adapted. For each dosage form and each trial separately, the quality of the video is rated as good, moderate or unusable, with moderate indicating that for example the video starts too late or does not have an optimal focus, and unusable indicating that videos are missing or performance cannot be evaluated at all. Thereafter, each step of the medication administration is scored on a 5-point Likert scale (5 = not possible, meaning practical assistance needed or interruption; 4 = severe difficulties, meaning execution hardly possible or success of therapy at risk; 3 = moderate difficulties, meaning execution significantly slowed down; 2 = mild difficulties, meaning execution slightly slowed down; 1 = no difficulties, meaning correct and fluid execution).

The following steps of medication administration were defined:For tablets: taking the white tablets out of the packaging, taking the blue tablet out of the packaging, cutting the blue tablet, putting all tablets correctly into the pill organizerFor eye-drops: opening the ophtiole dispenserFor oral drops: opening the dropper bottle, targeting at the teaspoon, correct number of drops on the teaspoonFor insulin pen: removing the cap from the pen, removing the cap from the needle, dialing in the right dose, injectionFor patch: opening the packing, peeling off protective liner, sticking onto the armFor inhaler: see Zambelli-Simões et al. [19]

Finally, a global impression of the ability to self-administer the respective dosage form is scored on a 5-point Likert scale (5 = very bad, 4 = bad, 3 = moderate, 2 = good, 1 = very good).

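### Test–retest reliability is to be assessed with Chi-square, which gives no reliability coefficient, and with Spearman's rho, which hides any systematic change in level

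*Protocol article*

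**What the plan says.** The section on video-based evaluation of self-administration provides for a retest: "In 30 patients the assessment is repeated after 5 days to assess test–retest reliability". The Statistical analysis section then fixes the method: "Retest reliability will be calculated using Spearman’s Rho for continuous variables and Chi-square for categorical variables". Nothing else in the article names an agreement coefficient, a test of mean change or limits of agreement for the retest.

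The main data concerned are ordinal, since "each step of the medication administration is scored on a 5-point Likert scale", running from 1 (no difficulties) to 5 (not possible). A global impression per dosage form uses a 1 to 5 scale as well. When describing the pilot with 15 raters, the Statistical analysis section treats single items as categorical and sum scores as continuous. On that reading, Chi-square applies to the retest of the items and rho to the retest of the sum scores.

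For the two raters of the full sample, the same paragraph chooses differently: "agreement will be evaluated with Cohen’s kappa for categorical data and intraclass correlation coefficient for continuous data". Tests are two-tailed at 0.05.

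**The concern.** Retest reliability asks whether the same patient gets the same score when nothing relevant has changed. Chi-square asks whether the two sets of ratings are independent, which is a much weaker question. It ignores which categories match. Rho compares rank orders only, so a change that moves all patients in one direction leaves little or no trace.

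The level of the score matters for the planned tool. The rating categories have absolute meanings, such as practical assistance being needed or the success of therapy being at risk. The article wants to use the tool to decide who needs support with medication. A patient who moves by a category may be classified differently even if the rank order is intact.

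A systematic change between sessions is plausible. Patients see an instructional video and perform every task except the inhaler twice in a session. They are in-patients of an orthopedic and trauma department, retested after 5 days. The Discussion names reliability among the qualities the tool should have, and the 30 repeat sessions exist to examine it. The stated statistics would not deliver that evidence for the items and would deliver only part of it for the sum scores.

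**Working it through.** The article gives no computed figure for retest reliability and no derivation of the 30 patients, so there is nothing to reproduce. The check is of what the named statistics can and cannot show.

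**Inputs from the article:** n = 30, 5-point ordinal items, alpha 0.05 two-tailed. **Assumed, because not given:** the distribution of ratings, the between-patient SD of sum scores and the size of any shift. All results below are therefore illustrative.

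**1. Chi-square cannot tell agreement from disagreement.** For a k×k table in which each first rating maps to exactly one second rating, chi-square = n(k − 1). Take 10 patients each at three ratings: 30 × 2 = 60 (df 4).
- Identical ratings (1→1, 2→2, 3→3): chi-square 60, kappa 1.
- Uniform one-category shift (1→2, 2→3, 3→4): chi-square 60, exact agreement 0/30. Chance agreement is 2 × (1/3 × 1/3) = 0.222, so kappa = (0 − 0.222)/(1 − 0.222) = −0.29.
- Full reversal (1→3, 2→2, 3→1): chi-square 60. Observed and chance agreement are both 1/3, so kappa = 0.

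For a binary item split 15/15, complete reversal gives chi-square 30 × 1 = 30 and kappa = −1.

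**2. Significance is a low bar.** In a 2×2 table chi-square = n × phi². The 5% critical value is 3.84, so phi = √(3.84/30) = 0.36 is enough. With equal margins at both sessions kappa equals phi, so a kappa of about 0.36 would count as significant. For scale, the article requires at least 0.8 before it accepts the pilot raters' agreement.

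**3. Illustration with improvement and a floor.** Practice or recovery would lower the ratings, and a patient already at 1 cannot improve. Let 10 patients each at 1, 2 and 3 become 1, 1 and 2.
- Chi-square: expected counts per row are 6.67 and 3.33. The sum is 2 × (3.33²/6.67 + 3.33²/3.33) + 6.67²/6.67 + 6.67²/3.33 = 2 × 5 + 6.67 + 13.33 = 30, df 2, p = exp(−15) = 3 × 10⁻⁷.
- Rho: first-session ranks deviate from their mean by −10, 0, 10 and retest ranks by −5, −5, 10. So rho = (50 + 0 + 100)/√(200 × 150) = 0.87. The plan would apply Chi-square to a single item; rho is shown for comparison.
- Exact agreement: 10/30.
- Kappa: chance agreement = 1/3 × 2/3 + 1/3 × 1/3 = 1/3, so kappa = (1/3 − 1/3)/(1 − 1/3) = 0.
- Quadratically weighted kappa: mean squared difference observed 20/30 = 0.667, expected by chance 12/9 = 1.333, so 1 − 0.667/1.333 = 0.50. The mean change is −20/30 = −0.67 category.

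**4. Sum scores.** If every patient shifts by d and the between-patient SD is s, without noise, rho is 1.00 at any d. The two-way, absolute-agreement, single-measure ICC is 1/(1 + (d/s)²/2):

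| Shift (SD) | rho | ICC, absolute agreement |
|---|---|---|
| 0.25 | 1.00 | 0.97 |
| 0.5 | 1.00 | 0.89 |
| 1 | 1.00 | 0.67 |
| 1.5 | 1.00 | 0.47 |
| 2 | 1.00 | 0.33 |

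A consistency ICC also stays at 1.00 throughout, so the type of ICC has to be named. With random error added (assumed error SD 0.35 of the true-score SD, shift of 1 true-score SD, 4,000 simulated samples of 30), mean rho is 0.86 and mean absolute-agreement ICC is 0.61.

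**The case against.** Several points on the other side are sound.

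- **Rank stability is a recognised sense of reliability.** If patients truly learn or recover, the change is real, and an absolute-agreement ICC charges it to the tool. For sum scores rho is therefore incomplete rather than wrong; what is missing is the change in level. This stands, and it is why the mean difference should be reported beside the ICC.
- **No shift is documented.** The article does not say that patients improve over 5 days, nor where the retest falls relative to surgery. The video and two performances in the first session could use up much of the practice effect beforehand. This stands: a shift is plausible, not established.
- **The contrast with the inter-rater analysis is limited.** The same paragraph uses Kendall's W, a rank-concordance measure, for the items in the 15-rater pilot, and it does not give the type of ICC. So the plan does not clearly handle level shifts elsewhere. It does show that agreement measures were available.
- **The retest is a small part of the study.** It involves 30 patients, is not among the listed main or secondary objectives, and the article foresees later validation in independent samples. This limits the damage but does not make Chi-square a reliability measure.

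A reader might infer that a tool whose scores shift for every patient would be reported as perfectly reliable. The documents do not support this. Chi-square reports no reliability value at all. Rho reaches 1.00 only when the shift preserves all ranks without noise; with a floor or with random error it was 0.87 and 0.86 in the examples above. Nor can the Chi-square p-value be called invalid outright. The average of 30/25 = 1.2 expected patients per cell applies only if all five categories are used at both sessions, and the distribution is unknown. Sparse tables are a caution only.

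**Conclusion.** The retest sentence is wrong as written for the categorical items and incomplete for the sum scores. Chi-square cannot provide a reliability estimate whatever the data turn out to be. That conclusion needs no assumption about a shift. Rho provides one aspect of reliability and leaves a systematic change unseen.

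How far the reported result would mislead depends on quantities that the article does not give. Under the assumed one-category improvement with a floor, a highly significant Chi-square goes with a kappa of 0. Under an assumed shift of 1 SD in a sum score, rho exceeds the absolute-agreement ICC by 0.33 without noise (1.00 against 0.67) and by 0.25 with the assumed noise (0.86 against 0.61). At a shift of 0.25 SD without noise the gap is only 0.03. If there is no systematic change, the problem with rho largely disappears and the problem with Chi-square remains.

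**What to change.** Replace the retest sentence in the Statistical analysis section before the analysis starts:

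- **Ordinal items and global impressions:** weighted kappa with a 95% CI, the weights stated in advance (for example quadratic), together with the change in ratings between sessions. The change is needed because weighted kappa was still 0.50 in the floor example, where two thirds of the patients moved.
- **Sum scores:** two-way, absolute-agreement, single-measure ICC with a 95% CI, plus the mean test–retest difference and limits of agreement, so that systematic change is shown separately from random error. Rho may be kept as a supplement.
- **Chi-square:** drop it as a retest measure.

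The cost is the rewording of one sentence and a little more analysis. The paired ratings are collected in any case, so no new data are needed. The downside is that the reported reliability will probably be lower than rho would suggest.

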### Study population

Eligible for inclusion in the study are patients ≥ 70 years of age regularly taking ≥ 5 different drugs autonomously who are admitted to the department of orthopedics and trauma surgery electively or via the emergency department. We intend to include 100 patients as a pilot sample to obtain a sufficiently large dataset for performing correlational and regression analyses. Since there is no previous evidence, it was not possible to perform sample size calculation for our specific research question. The only previous study analyzing a related research question, which observed that the ability of geriatric patients to open pill packaging was significantly associated with vision, cognitive function, and manual dexterity [9], recruited a similar sample size as planned in or study (n = 119). Patients are recruited continuously until the planned sample size is reached. Study participation is voluntary and does not affect further treatment.

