#### Measures

##### Patient characteristics

In a face-to-face interview, the following patient characteristics are assessed:Sex (male, female, diverse)Age (years)Body weight (kg)Height (cm)Handedness (right, left, ambidextrous)Housing situation (single-person household, multi-person household, nursing home)Marital status (open response format, later classified as single = never married, married = living together with a partner, living apart = married but separated, widowed)Education level (open response format, later classified according to International Standard Classification of Education [10])Last profession (open response format, later classified according to International Standard Classification of Occupations [11])Reason for the current hospitalization (open response format, later classified according to the German modification of the International Classification of Procedures in Medicine [OPS])

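### Chi-square is prescribed for nominal factors against continuous ability scores with no categorisation of the score, so this bivariate test does not fit its data

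*Protocol article*

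**What the plan says.** The Statistical analysis section sets out the bivariate step by type of factor. The sentence opens with the outcome, "For continuous scores describing the ability to self-administer medication", and continues: "Spearman’s Rho will be used for analyzing continuous and ordinal factors and Chi-square for analyzing nominal factors". No grouping of the score is mentioned for the Chi-square part.

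What counts as continuous is clear from the preceding paragraph of the same section, which plans the "intraclass correlation coefficient for continuous data (sum scores"). Under Video-based evaluation of self-administration of medication, "each step of the medication administration is scored on a 5-point Likert scale", so the natural scores are sums of items rated 1 to 5.

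The same paragraph then plans univariable and multivariable linear regression with interaction terms to find which factors influence ability and how strongly. All tests are two-sided, with significance at p < 0.05. Under Study population the article says "We intend to include 100 patients as a pilot sample" and that "it was not possible to perform sample size calculation for our specific research question".

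**The concern.** Pearson's Chi-square treats both variables as unordered categories. Applied to a sum score, it makes every distinct value a category of its own. It ignores that 30 is closer to 31 than to 70, and it spreads 100 patients over a very large table. The article names a particular test for a particular type of outcome and the two do not match, so this is not detail left to a fuller document: a fuller plan would have to contradict the sentence or add a categorisation that the sentence does not hint at.

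Identifying factors associated with the ability to self-administer medication is one of the main objectives. The nominal factors touched are sex, handedness, housing situation, marital status, last profession and reason for hospitalisation (Patient characteristics), and success in opening a bottle (Motor function/functional state). A real difference on one of these could go unseen at the bivariate step.

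**Working it through.** The plan has no power figure to reproduce. The only design figure is N = 100.

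**Inputs from the article.** N = 100; two-sided alpha 0.05; steps rated 1 to 5; listed steps without the inhaler 4 + 1 + 3 + 4 + 3 = 15, so one trial sums to between 15 and 75. Tablets alone, or the insulin pen alone, have 4 steps, range 4 to 20.

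**Assumptions, not in the article.** Latent effect 0.5, 0.6 or 0.8 SD; ratings skewed towards no difficulties; item loading 0.6 (15-step score); group sizes as shown below; no missing data. The article does not say how the analysed ability score is composed, so two versions are shown.

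**Exact case: all scores distinct.** Each score column holds one patient. For a patient in group g of size n_g, the column contributes N/n_g − 1. Summed over patients:

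chi-square = Σ n_g (N/n_g − 1) = N(k − 1), on (k − 1)(N − 1) df.

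- k = 2: 100 on 99 df, p = 0.45
- k = 3: 200 on 198 df, p = 0.45
- k = 4: 300 on 297 df, p = 0.44

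The result is the same whatever the group difference, so the test carries no information about the factor.

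**With ties.** The 15-step sum took about 28 to 35 distinct values among 100 patients. That is 100/35 = 2.9 to 100/28 = 3.6 patients per value, or about 1.4 to 1.8 expected per cell with two equal groups. Between 95 and 100% of cells had an expected count below 5; for the four-step sum, about 70%.

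**Simulated power** for latent effects of 0.5, 0.6 and 0.8 SD (1500 runs per setting for the 15-step score, 3000 for the four-step score; Monte Carlo standard error at most √(0.25/1500) = 0.013):

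| Score, group sizes | Chi-square, uncategorised score | Mann-Whitney / Kruskal-Wallis | Chi-square after median split |
|---|---|---|---|
| 15 steps, 50/50 | 0.04, 0.06, 0.13 | 0.61, 0.75, 0.94 | 0.50, 0.62, 0.83 |
| 15 steps, 30/70 | 0.01 to 0.06 | 0.53 to 0.91 | 12 to 16 points below Mann-Whitney |
| 15 steps, 45/45/10 | 0.103, 0.137, 0.183 | 0.235, 0.321, 0.527 | 0.155, 0.232, 0.362 |
| 15 steps, 40/35/15/10 | 0.111, 0.133, 0.185 | 0.214, 0.259, 0.427 | 0.157, 0.189, 0.285 |
| 4 steps, 50/50 | 0.14, 0.20, 0.38 | 0.53, 0.69, 0.91 | not run |

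Check of the simulation: for a purely continuous score in two groups of 50, the t-test formula gives 0.705, 0.851 and 0.979; the simulation gave 0.688, 0.845 and 0.975.

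**Reading the table.**
- Three levels: relative loss from 1 − 0.103/0.235 = 0.56 to 1 − 0.183/0.527 = 0.65.
- Four levels: from 1 − 0.111/0.214 = 0.48 to 1 − 0.185/0.427 = 0.57.
- Median split, 50/50: 0.61 − 0.50 = 0.11, 0.75 − 0.62 = 0.13, 0.94 − 0.83 = 0.11. Quartiles (0.39, 0.54, 0.81) lose 13 to 22 points.

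**Type I error.** For Chi-square on the uncategorised score it was 3.2% with the four-step sum, and 4.1% and 3.1% with the 15-step sum and three or four levels. The nominal level is 5%.

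**The case against.** The strongest reply is that the gap is already covered. Univariable linear regression on a dummy-coded nominal factor is a t-test or ANOVA on the continuous score, with an estimate and a confidence interval, and the article gives those regressions the task of identifying influential factors. This stands, and it bounds the harm. A reader might infer that real differences on every nominal factor would be missed. The article does not support that: Chi-square is not the only planned test, and nothing says that its result decides which factors enter the regressions.

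The authors may also intend to group the score first; the preceding paragraph pairs Chi-square with categorical variables. That is possible, and most of the power would then be kept, so a general claim that the test discards most of the power goes too far. But no grouping is stated, and a cut-point left open can be chosen after the data are seen.

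A reader might further infer from the sparse table that false positives will multiply. The simulated type I error is below 5%, so the test is conservative and what is shown is lost sensitivity.

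Finally, this is an observational pilot sample without a power claim, and the effect sizes and score structures above are assumed. That is right, and the percentages are illustrations rather than the trial's own figures. The mismatch between test and data does not depend on them.

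**Conclusion.** The sentence is wrong as written: it pairs a continuous outcome with a test for two categorical variables. Followed literally, the test is uninformative if all scores differ and weak if they are tied. For two-level factors most of the power is lost with the 15-step score and more than half with the four-step score; for three or four unequal levels, about half to two thirds. These sizes rest on the assumed effects, score composition and group sizes, and the figures for several levels also depend on which levels differ.

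The damage stays in the bivariate step. What remains is that the plan holds two tests of the same association, both read at p < 0.05, with no rule for when they disagree. A two-level factor could be clearly associated in univariable regression and give p near 0.45 on Chi-square. This should be fixed, but it does not undermine the study.

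**What to change.** Replace the Chi-square part of the sentence. For nominal factors against ability scores, use Mann-Whitney U (two levels) or Kruskal-Wallis (three or more), with an effect size and confidence interval. A t-test or ANOVA serves equally well and coincides with the planned univariable regression under dummy coding; if that route is taken, say that the regression is the bivariate test. Keep Chi-square or Fisher's exact test for pairs of categorical variables. If a categorised score is really meant, state the categories before the data are analysed and accept the loss of power.

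State in advance how sparse levels will be collapsed, above all for last profession and reason for hospitalisation. With 100 patients, Kruskal-Wallis also suffers from very small groups.

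The cost is a sentence or two, plus the decision on collapsing levels. No further data are needed, and the article reports recruitment under way with the analysis still to come.
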